## Abstract

**Background:**

Chronic venous leg ulcers (CVLUs) are the most common type of lower extremity wound. Even when treated with evidenced-based care, 30–50% of CVLUs fail to heal. A specific gap exists about the association between psychosocial stressors, particularly loneliness, and biomarkers of inflammation and immunity. Loneliness is highly prevalent in persons with CVLUs, has damaging effects on health, and contributes to the development of multiple chronic conditions, promotes aberrant inflammation, and diminishes healing. However, the confluence of loneliness, inflammation and the wound healing trajectory has not been elucidated; specifically whether loneliness substantially mediates systemic inflammation and alters healing over time. This study seeks to address whether there is a specific biomarker profile associated with loneliness, CVLUs, and wound healing that is different from non-lonely persons with CVLUs.

**Methods:**

An observational prospective study will identify, characterize and explore associations among psychosocial stressors, symptoms and biomarkers between 2 CVLU groups, with loneliness+ (*n* = 28) and without loneliness- (*n =* 28) during 4 weeks of wound treatment, measured at 3 time points. We will examine psychosocial stressors and symptoms using psychometrically-sound measures include PROMIS® and other questionnaires for loneliness, social isolation, depression, anxiety, stigma, sleep, fatigue, pain, quality of life, cognition, and function. Demographics data including health history, sex, age, wound type and size, wound age, and treatment will be recorded from the electronic health record. We will characterize a biomarker panel of inflammatory genes including chemotaxic and growth factors, vascular damage, and immune regulators that express in response to loneliness to loneliness and CVLUs using well-established RNA sequence and PCR methods for whole blood samples. In an exploratory aim we will explore whether age and sex/psychological stressors and symptoms indicate potential moderation/mediation of the effect of loneliness on the biomarker profile over the study period.

**Discussion:**

This study will provide insight into the influence of psychosocial stressors, symptoms, and biological mechanisms on wound healing, towards advancing a future healing prediction model and interventions to address these stressors and symptoms experienced by persons with CVLUs.

## Background

It is well established that individuals with chronic wounds, particularly those with chronic venous leg ulcers (CVLUs), have substantially reduced quality of life [1–3]. A wound is defined as chronic when it fails to reduce in size by 50% for at least 6 weeks after onset [4]. Up to 150 million individuals worldwide live with slow or non-healing ulcers. This is problematic because CVLUs account for ~ 80% of all chronic ulcers [5] that take months to years to heal [6]; for those that do heal, as many as 70% recur within 3 months [7].

Most CVLUs are associated with physical, psychological, and social symptoms. Physically, people with CVLUs experience symptoms such as odor, drainage, and leg swelling, which affect functional ability and physical appearance [8]. Self-management of CVLUs has been linked to^,^ fatigue and pain [9], and physical exhaustion [10] from the intense care required. Psychological symptoms reported by people with CVLUs include fear that the ulcer will never heal, will get infected, or that an amputation may occur [1, 10]. In the literature, cognitive dysfunction, poor self-image and worry [1], depression and anxiety have been reported [9]. These physical and psychological symptoms are known to negatively influence mobility, sleep, and mood, and limit professional, familial and social relationships, especially contact with friends [11]. Frequent and prolonged care is reported to lead to feelings of anger and resentment [12].

It is possible that sex, psychosocial stressors, and symptoms play a predominant role in perpetuating a chronic, non-healing state yet these factors are understudied, rarely assessed, and not consistently managed during clinical encounters. It is concerning that 30–50% of CVLUs fail to heal, even when treated based on best clinical practices which include: compression and leg elevation to improve venous blood flow, wound dressings to control necrotic tissue and wound exudate, and advanced topical biological therapies such as skin substitutes and growth factors to alter the local wound environment [13]. In the past 10 years, two studies have discovered that males with CVLUs report higher scores for both depression and anxiety [14, 15]. The findings regarding sex and associated symptoms underscore the critical need to explore the psychosocial and biological mechanisms that influence wound healing [16].

A specific gap exists when seeking knowledge about the association between psychosocial stressors, particularly loneliness, and biomarkers of inflammation and immunity. Loneliness has damaging effects on health, and contributes to the development of multiple chronic conditions [17], and diminished healing. Population-based longitudinal research indicates that loneliness predicts functional decline, morbidity and mortality, independent of objective social isolation, depression and health behavior [18, 19]. Loneliness is defined as a distressing feeling that accompanies the perception that one’s social needs are not being met by the quantity (social isolation) or especially the quality of one’s social relationships with individuals and/or the community [17, 20–23]. Loneliness affects ~ 50% of older adults in the U.S. [24], 68% of older adults with chronic wounds [25], and is associated with cardiovascular disease, hypertension, stroke, cancer, functional disability, and cognitive decline [26–28]. The negative health effects of loneliness exceed those of cigarette smoking, physical inactivity, and obesity [17, 29–31].

A growing body of evidence indicates wound healing is substantially altered by loneliness and social isolation in both human and animal models [32–34]. Loneliness is associated with altered molecular mechanisms such as inflammation and increased levels of pro-inflammatory cytokines [35], that may impede wound healing [36–38]. In addition, exposure to psychosocial adversity has been shown to elicit vascular, neuroendocrine physiological responses including increased peripheral resistance and dysregulation of the hypothalamic-pituitary adrenocortical (HPA) axis [38].

A growing literature in human social genomics suggests that psychosocial adversity and a negative social environment are associated with differential expression of hundreds of gene transcripts involved with inflammation and antiviral response, known as the *conserved transcriptional response to adversity* (CTRA) pathway. Loneliness has been associated with up-regulated inflammation by enhancing the transcription of genes such as interleukin-1 alpha and beta, interleukin-6, interleukin-8, cyclooxygenase 2, and tumor necrosis factor [39, 40] and the potent pro-inflammatory NF-kappa B gene [41]. The CTRA pathway is characterized by decreased expression of Type I interferon-related antiviral genes and increased expression of proinflammatory genes. However there is a paucity of literature to determine whether these same genes are also expressed in individuals with loneliness and chronic wounds [42]. The premise of this study is that a ~ 50-gene composite score previously used to assess the CTRA profile will be up-regulated in lonely (L+) individuals with CVLUs supporting the link between chronic wounds and inflammatory genes [43, 44]. The overexpression of these wound-related genes, in particular inflammatory cytokines may be considered candidates for the prediction of treatment response among patients with L+ and CVLUs. Experimental studies in animal and human models show a causal impact of adverse social conditions on CTRA gene expression [45]. Specific to chronic wounds, systemic inflammation is a well-established biological pathway linked to poor wound healing outcomes and is the focus of our study.

Recognizing that inflammatory biomarkers such as elevated cytokines and altered gene expression exist in CVLUs, we hypothesize that substantially heightened inflammation is a common molecular mechanism with a distinct profile that underlies both loneliness and poor wound healing in a chronic wound population compared to a wound population without loneliness. However the confluence of loneliness, inflammation and the wound healing trajectory has not been elucidated; specifically whether loneliness substantially mediates systemic inflammation and alters healing over time. The major question this study seeks to address towards advancing wound and symptoms sciences is whether there is a specific biomarker profile associated with loneliness, CVLUs, and wound healing that is different from non-lonely patients with CVLUs by addressing the following aims:

### Aim 1

Examine whether psychosocial stressors (i.e., social isolation, social support) and symptoms (i.e., fatigue, pain, depression, anxiety, sleep disturbance, reduced QOL) differ between (L+) and (L-) patients with CVLUs using well-validated questionnaires.

### Aim 2

Characterize a biomarker (chemotaxic factors, growth factors, vascular damage and immune regulators) profile common to loneliness and CLVU using well-established RNA sequencing and PCR methods for whole blood samples. We will start the analysis using a 1.8-fold change in gene expression, either positive or negative, to generate a composition score to assess the effect of loneliness and stressors on biomarkers.

### Exploratory aim 3

Explore whether age and sex/psychological stressors and symptoms indicate potential moderation/mediation of the effect of loneliness on the biomarker profile over the study period.

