
#### Analyses for aim 2

All RNA sequencing will be performed at the UCLA Social Genomics Core Lab. RNA will be extracted from PAXgene tubes (Qiagen RNeasy), tested for suitable mass and integrity, and converted to cDNA libraries using a high-efficiency enzyme system (Lexogen QantSeq 3′ FWD). Normalized cDNA libraries will be sequenced using an Illumin HiSeq 4000 instrument, targeting > 10 million reads per sample. Reads will be aligned to the reference human transcriptome and quantified as gene transcripts per million total mapped reads using the STAR aligner. Transcript abundance data will be log2 transformed for analysis by linear statistical models quantifying differential gene expression as a function of key predictors (e.g., loneliness wound healing) while controlling for potential confounders, particularly age, sex, race/ethnicity, BMI, smoking history, and heavey alcohol consumption history. The CTRA will be measured by a pre-specified 53-gene composite score used in previous social genomics studies, [48, 49] including 19 gene transcripts involved in inflammation (i.e., *IL1B, IL6, IL8, TNF*), 34 gene transcript involved in innate antiviral responses (*IFNB, IFI-, MX-,* and *OAS-*family genes). Scores will be composed by z-score standardizing expression of each gene and summing the resulting values after sign-reversing the antiviral genes to reflect their inverse contribution to the CTRA profile.

#### Analyses for aim 3

The goal of aim 3 is to explore whether age and sex/psychological stressors and symptoms indicate potential moderation/mediation of the effect of loneliness on the biomarker profile over the study period. The composite score of the biomarker expression values will be used as the dependent variable for this analysis. Subsequently, to compensate for the limited sample size of this exploratory analysis, a bootstrapping procedure that resamples the data with replacement will be employed to provide more accurate estimates of variability (95% CIs). The analysis will involve a comparison of the composite score between L+ and L- using MEM as described above. Moderators will be explored through inclusion of an interaction term in the model, for example, age-by-loneliness. Potential mediators will be explored individually using MEM. Exploratory analyses will follow the modified procedure suggested by MacKinnon, Fairchild & Fritz [48] of the causal steps approach developed by Baron & Kenny [50].

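### Aim 2 builds its score from a 1.8-fold change, the analysis section uses a fixed 53-gene score, and Aim 3 does not say which one is compared by loneliness; if the fold change is L+ versus L-, the first is circular

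*Protocol article*

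**What the plan says.** The Aim 2 statement, at the end of the Background, says: "We will start the analysis using a 1.8-fold change in gene expression, either positive or negative, to generate a composition score". The purpose given is "to assess the effect of loneliness and stressors on biomarkers". It concerns four marker classes (chemotaxic factors, growth factors, vascular damage, immune regulators), which are itemised under Table 1.

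Analyses for aim 2 takes another route: "The CTRA will be measured by a pre-specified 53-gene composite score used in previous social genomics studies". Membership is fixed, "including 19 gene transcripts involved in inflammation" and "34 gene transcript involved in innate antiviral responses", and so is the arithmetic: "Scores will be composed by z-score standardizing expression of each gene and summing the resulting values after sign-reversing the antiviral genes". No fold-change cut appears there.

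Analyses for aim 3 says: "The composite score of the biomarker expression values will be used as the dependent variable for this analysis". It continues: "The analysis will involve a comparison of the composite score between L+ and L- using MEM as described above". It does not say which of the two scores is meant.

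**The concern.** The two rules differ in kind. The CTRA score fixes genes and signs before any data are seen. The Aim 2 rule lets the study data choose the genes. The comparison behind the 1.8-fold change is not named, but the score is meant to assess loneliness and L+ and L- are the only two groups in the design, so L+ versus L- is the obvious candidate. On that reading the same 56 people both select the genes and supply the test. No split sample, cross-validation or external sample is described.

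At stake is the biomarker outcome for Aims 2 and 3: either a pre-specified score with a valid test, or a data-driven score whose group comparison has no error control. The Conclusion hopes that a biomarker difference will lead towards a prognostic indicator of healing, so a difference produced by selection would be carried forward.

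**Working it through.** **1. The plan's own figure.** 19 inflammatory + 34 antiviral = 53. The gene count of the fixed score reproduces.

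**2. The three places side by side.**

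| Place | How genes enter the score | Signs | Use |
|---|---|---|---|
| Aim 2 statement | 1.8-fold change, up or down; contrast not stated | not stated | effect of loneliness and stressors |
| Analyses for aim 2 | fixed list of 53 | fixed (antiviral reversed) | CTRA measure |
| Analyses for aim 3 | not stated | not stated | L+ versus L- comparison |

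**3. What passing the cut implies, if the contrast is L+ versus L-.** Expression is analysed on the log2 scale, and log2(1.8) = 0.848. With 28 per group, the standard error of a mean difference is SD × √(1/28 + 1/28) = 0.267 × SD. The two-sided 5% critical value of t on 54 degrees of freedom is 2.005, so one gene is significant alone when its difference exceeds 2.005 × 0.267 × SD = 0.536 × SD. Any gene with SD below 0.848 / 0.536 = 1.58 that passes the cut is therefore already significant at 5%. Testing it again by loneliness repeats the selection.

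**4. How often a gene passes under the null.** The protocol gives no gene SD, so the values are assumed. The chance per gene is 2 × [1 − Φ(0.848 / (0.267 × SD))].

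| log2 SD | Chance per gene | Expected passes among 53 |
|---|---|---|
| 1.0 | 0.15% | 53 × 0.0015 = 0.08 |
| 1.5 | 3.4% | 53 × 0.034 = 1.8 |
| 2.0 | 11.3% | 53 × 0.113 = 6.0 |

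**5. Null simulation.** There are 28 per group, no true loneliness effect, and between-gene correlation 0 or 0.3. Genes passing the cut on L+ minus L- are z-scored, summed with their observed signs, and compared between groups by a two-sided t-test at 5% in the same patients. Overall false-positive rates were:

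| Candidate genes (assumed) | SD 0.5 | SD 0.75 | SD 1.0 | SD 1.5 | SD 2.0 |
|---|---|---|---|---|---|
| 53 | 0% | 0.1–0.2% | about 7% | 69–83% | 94–99% |
| 1,000 | 0% | 2–3% | 45–78% | 100% | 100% |
| 10,000 | 0% | 9–19% | 94–100% | 100% | 100% |

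The near-zero entries do not show good error control. No gene passes there, so there is no score to test.

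Among the 53-gene null studies in which a score exists, the test rejects in roughly 87–100% with observed signs, including settings where SDs vary between genes. If the selected genes instead take their fixed CTRA signs, it rejects in about 46–100%, falling to about a third when every gene has SD 2. The fixed 53-gene score rejects in about 5% throughout.

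**6. The other contrast.** If genes are selected on change from V1 to V3 pooled over both groups (53 genes, within-patient correlation 0.4 assumed), overall false positives stay under 1% for SD 1 to 2. This is not only because few genes pass. In a check of 2,000 null studies per setting, at SD 2 a gene passed in 14–19% of studies, and the score was significant by loneliness in 3–4% of those. Selection that ignores the loneliness label does not bias the loneliness test.

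These simulations use a simple t-test. The plan uses mixed models over three visits with covariates, so the percentages are indicative.

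**The case against.** The strongest reply is that there may be two separate scores: one from the four-class panel under Table 1, to which the Aim 2 wording belongs, and the CTRA score. Aim 2 speaks of a *composition* score. Aim 3 speaks of a *composite* score and follows directly after the paragraph defining the 53-gene composite, and the Background premise is also a composite of about 50 genes from earlier work. On this view Aim 3 already tests the fixed score, and the 1.8-fold step is only a screen to begin with. This has weight, and a reader should not conclude that Aim 3 certainly tests a fold-change score. But the text never says there are two scores, Aim 3 describes its outcome only as a score of the biomarker expression values, and Aim 2 gives the fold-change score the job of assessing loneliness.

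A reader might also infer that a positive result is guaranteed. The documents do not support that. The contrast and the sign rule are not stated, the rejection rate falls well short of 100% in some settings, and the overall rate runs from 0% to 100% depending on gene SDs and a candidate list that the protocol does not give.

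The study calls itself small and exploratory, which softens the consequence. It does not validate a test that rejects because of how its outcome was selected, and among the aims only Aim 3 carries that label.

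Finally, the 34 to 19 balance of antiviral and inflammatory genes might be read as a flaw in the score. It is not an error: the Background defines CTRA by both components.

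**Conclusion.** The point holds in conditional form. It is certain from the text that the Aim 2 statement and the Aim 2 analysis describe different ways to form a score, that the fold-change contrast is missing, and that Aim 3 does not identify its dependent variable. The circularity rests on one inference, that the 1.8-fold change is L+ versus L-. The score's stated purpose makes this the natural reading, but it is not written. On that reading, a loneliness test of the selected score in the same patients rejects far too often under the null whenever a score exists, against about 5% for the fixed score, and at low gene SD there may be no score at all. On a pooled change-over-time reading the bias largely goes, and what remains is a conflict to reconcile. The 53-gene score itself is sound on this point.

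**What to change.** In the Aim 2 statement, remove the 1.8-fold rule as a way to build a tested score. Name the pre-specified 53-gene CTRA score as the composite compared between L+ and L-. In Analyses for aim 3, name the same score as the dependent variable.

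Any 1.8-fold gene list, including one drawn from the Table 1 panel, can stay as description, with its contrast stated and false-discovery-rate q-values given. A score built from that list should not be tested for loneliness in the same sample without cross-validation that repeats the gene selection within each fold.

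Reporting the 19-gene and 34-gene sub-scores is optional.

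The cost is wording in two places and no new data. The loss is a flexible data-driven score.

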## Methods/design

### Overall strategy

The overarching aims of this observational prospective study are to identify, characterize and explore associations among psychosocial stressors, symptoms and biomarkers (panel of inflammatory genes that express in response to loneliness) between 2 CVLU groups, L+ (*n* = 28) and L- (*n =* 28) during wound treatment at 3 time points – baseline (V1), end of month 1 (V2) and end of month 2 (V3) - over a 2-month period. Eligibility criteria include: female and male; ≥ 60 years of age; CVLU of ≥6 weeks duration, and English speaking. Patients will be excluded if they are undergoing chemotherapy (affects immune factors), or taking steroids (may decrease inflammation and affect cytokine levels). We do not want to exclude participants based on wound treatment because the point of the proposal is to better understand loneliness in people with wounds. We are collecting treatment data but it will not determine inclusion. We also want to characterize participants by loneliness based on treatment but in order to do that, we will need to do a subsequent adequately powered study to determine the influence of treatments. Demographic and health data will be obtained from participants and the electronic health record. All participants will be recruited from the local wound communities/wound clinics in the southeastern region of the U.S.

Participant compensation will be provided. In return for their time and effort, each participant will receive a check for $25.00 for each completed study visit. Checks will be mailed to the address that the participant provides to the researchers. Additionally, we will offer a “fish bowl” prize drawing at each visit in which patients can “win” an additional $1 to up to $25 at V2 and V3 – we have used this contingency management strategy in our previous wound prevention studies with great success (7% attrition rate in a recently completed randomized controlled trial). The odds for the prize drawing are devised so that participants will not in all likelihood receive disproportionate amount of study compensation. A CONSORT diagram of participant flow through the study is provided below in Fig. 1.

**Fig. 1 Fig1:**
[figure not shown]
CONSORT diagram of participant flow in the study

### Demographics

Age, race, ethnicity, sex, marital status, education, disability status, income (socioeconomic status), and employment information will be collected by study personnel and recorded on the investigator-generated study specific demographics form developed for use in our previous studies. We will enter all data for the 3 visits into our study database in REDCap, a secure electronic documentation data storage management system. There are known sex differences in the neuroendocrine stress response and in the prevalence, symptoms, and correlates of loneliness in adults [46]. In our prior studies we reported that, in older adults, female sex was predictive of loneliness yet in rural areas such as Appalachia, mid-life men had higher mean loneliness scores [47]. Therefore, it is likely that loneliness impacts the health of males and females differently, making it critical to include sex as a biological variable in the study design. We will attempt to recruit equal numbers of males and females per loneliness group (L+ vs L-). Though no sex-specific hypotheses will be tested in the proposed study, we plan to explore possible differences of the effect of loneliness by sex (moderation) in the analyses, for example, through inclusion of sex-by-interaction terms). As this study is not powered to confirm hypotheses regarding moderating effects, these analyses will be considered hypothesis generating and descriptive rather than hypothesis testing. Per NIH guidelines, we will also report outcomes separately by sex.

